### 3.10 Withdrawal Criteria

All participants are strongly encouraged to complete the study, however there may be certain situations in which withdrawal from the study may be appropriate. Participants may withdraw from the study if one or more of the following occurs:

- The participant experiences any serious adverse event (SAE) or reaction due to the use of varenicline or NRT lozenges. Prior to treatment discontinuation, input from the treating medical team and end point evaluation committee will be sought in establishing the association between treatment exposure and adverse events. The DSMB will review all such cases and make the final judgement on causality.
- If a female participant becomes pregnant during the course of treatment
- If a participant's health status changes significantly and the study medications are no longer in the best interest of the participant
- The lead investigators or health professionals perceive, for any reason, that the study is no longer in the best interest of the participant

A participant wishing to withdraw from the study will be requested to fill a 'withdrawal form' for record purposes. Once withdrawn, the participant will not be contacted for further data collection, however their available data will be included in the Intension-to-treat analysis. If withdrawal is a result of an adverse drug reaction, the participant will be followed until the adverse reaction resolves or there is return to clinically acceptable medical status.

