### 4.2 Data Analysis

Data will be stored in a suitable database (e.g. REDCap™, ACCESS™) and exported for analysis in Statistical Package for Social Sciences (SPSS) (version 23.0; IBM, Armonk, NY) and Stata (ver 15, StataCorp, College Station, TX). As recommended by the Russell Standard, all randomised patients will be accounted for in the intention to treat (ITT) analysis. Participants with missing outcomes at follow-up or whose self-reported abstinence was not biochemically validated will be considered as smokers. Sensitivity analyses using multiple imputation methods will also be carried out. Deceased participants will be excluded from

analyses. In a supportive analysis of the primary efficacy endpoint, an analysis will also be conducted on the per protocol set, which excludes patients with any major protocol deviations.

Logistic regression analyses will be used to examine the efficacy of intervention on the primary outcome, after testing homogeneity between hospitals using a random effects meta-analysis. In the event of heterogeneity, a more robust model incorporating clustering by hospital will be fitted. The effect of intervention on continuous abstinence at 6 months will be tested in pre-specified subgroups (per hospital, nicotine dependence, highly motivated versus moderately motivated smokers and men versus women) using models fitted for each subgroup containing main effects for intervention and subgroup and an interaction between them. Statistical significance will be considered at a two-sided p value of 0.05.

All randomised participants who take at least one dose of the treatment medications will be included in the safety analysis. A chi-squared test will be done to compare the frequency of treatment withdrawal between the treatment and comparator arms. The number of participants discontinuing treatment prematurely for any reason will be summarised by treatment group and by reasons for discontinuation.

The incidence of all suspected adverse events will be summarised by treatment group under the following categories: type, severity, action taken and outcome. Severity of adverse events will be reported using the CTEAE grading scale (v5.0). The causality of the adverse events will be determined using the Noranjo algorithm.

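### Section 3.10 mixes stopping study medication with leaving the study, which can create avoidable missing 6-month outcomes that are then scored as smoking

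*Combined protocol and SAP*

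**What the plan says.** Protocol section 3.10 introduces its list with "Participants may withdraw from the study if one or more of the following occurs". There are four grounds:

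- a serious adverse event (SAE) or reaction due to varenicline or the lozenges
- pregnancy during treatment
- a change in health such that "the study medications are no longer in the best interest of the participant"
- a view among lead investigators or health professionals that the study itself no longer serves the participant

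A participant who wishes to leave is asked to complete a form. The section continues: "Once withdrawn, the participant will not be contacted for further data collection". It adds that "their available data will be included in the Intension-to-treat analysis". The one exception to the end of contact is for safety: "If withdrawal is a result of an adverse drug reaction, the participant will be followed until the adverse reaction resolves", or until clinical status is acceptable.

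Section 4.2 sets the scoring: "Participants with missing outcomes at follow-up or whose self-reported abstinence was not biochemically validated will be considered as smokers". It also states "Sensitivity analyses using multiple imputation methods will also be carried out" and "A chi-squared test will be done to compare the frequency of treatment withdrawal between the treatment and comparator arms", and plans a summary of premature discontinuation by arm and reason. The SAP keeps intention to treat with losses counted as smokers. Its text does not mention multiple imputation.

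**The concern.** Stopping a drug and leaving a trial are different events. Someone taken off varenicline or lozenges for safety can still answer a telephone call and give a breath sample, and an intention-to-treat comparison needs that result. Section 3.10 puts drug-stopping reasons under study withdrawal and then ends outcome contact. Staff could reasonably read it as telling them to stop calling such a person.

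If they do, the 6-month CO result does not exist and section 4.2 makes the participant a smoker. Section 3.8 applies that label only after ten contact attempts and an approach to next of kin. Under 3.10 it would apply to people nobody tried to reach.

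If these withdrawals differ by arm, tolerability enters the abstinence comparison. An excess in the combination arm would lower its apparent benefit, and an excess in the control arm could raise it. Appendix C gives a reason to think of imbalance: nausea is listed as common with varenicline and very common with nicotine lozenges, and only the combination arm takes both.

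**Working it through.** **Text, step by step**

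1. *Grounds.* Three of the four are reasons to stop medication. The first is itself worked through in terms of treatment discontinuation, although the list is headed as study withdrawal. The fourth is a study-level judgement.
2. *Contact.* After withdrawal there is none for data collection. Safety follow-up of a reaction does not include smoking status or a CO test. Data already collected are kept, but they cannot supply a 6-month CO result.
3. *Timing.* Treatment lasts 12 weeks, or 24 with extension (sections 3.5.1 and 3.5.2). The primary outcome covers weeks 2 to 26 (section 3.9.2). A withdrawal during treatment therefore comes before the primary CO test.
4. *Scoring.* The missing outcome counts as smoking (section 4.2).
5. *Rescue clause.* Nowhere do the documents say that a participant who stops medication stays in outcome follow-up.

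**The plan's own figure**

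Inputs from sections 4.1 and 4.2: 23% against 38% (23 + 15), two-sided 5%, 80% power, 1:1 allocation. The mean rate is 0.305.

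- Uncorrected: n0 = [1.960 × √(2 × 0.305 × 0.695) + 0.842 × √(0.23 × 0.77 + 0.38 × 0.62)]² / 0.15² = 146.7, so 147 per arm.
- With continuity correction: n = (n0/4) × [1 + √(1 + 4/(n0 × 0.15))]² = 159.8, so 160 per arm.

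The stated 160 is reproduced. The documents describe no inflation for withdrawal.

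**Illustration of size**

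The documents give no withdrawal rate. These inputs are assumptions:

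- wT and wC are the proportions withdrawn before 6 months in the combination and control arms.
- q is abstinence among the withdrawn relative to their arm's planned rate, taken as 0.5 to 1.

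One abstainer scored as a smoker moves an arm by 1/160 = 0.625 points.

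Ten withdrawals in one arm (10/160 = 6.25%):

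- Combination: 10 × 0.38 × q = 1.9 to 3.8 abstainers, or 1.19 to 2.38 points.
- Control: 10 × 0.23 × q = 1.15 to 2.3 abstainers, or 0.72 to 1.44 points.

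Observed difference in points = 15 − q × (38 × wT − 23 × wC):

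| Combination / control withdrawn | q = 0.5 | q = 1 |
|---|---|---|
| 2% / 2% | 14.85 | 14.70 |
| 5% / 5% | 14.63 | 14.25 |
| 10% / 10% | 14.25 | 13.50 |
| 10% / 5% | 13.68 | 12.35 |
| 5% / 10% | 15.20 | 15.40 |

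With no true effect (23% in both arms), q = 1 and 10% / 5% withdrawn, the spurious difference is 23 × (0.05 − 0.10) = −1.15 points, against the combination.

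**The case against.** The strongest reply is that 3.10 describes voluntary departure. It says participants may withdraw, and the no-contact sentence follows one about a participant who wishes to leave. The sentence on adverse reactions fits a person who asks to leave because of a reaction. Elsewhere the protocol treats stopping the drug as a separate matter. Section 6 speaks of discontinuing treatment after safety concerns without mentioning departure from the study. Section 3.5.3 handles intolerable nausea by checking how the tablets are taken and, if needed, lowering the dose. The follow-up visits in section 3.8 are not conditional on taking medication.

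Much of this stands. A reader might infer that everyone who stops medication is dropped from follow-up and fails the primary outcome by rule. The documents do not support that, because nothing makes withdrawal automatic. What remains is that drug-stopping grounds are listed as grounds for leaving, that one ground rests on clinicians' judgement and not the participant's request, and that no sentence rules out ending contact with someone who has not refused it.

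It is also fair that counting missing as smoking is a declared convention, applied alike to both arms. The point does not dispute it for people who refuse contact or cannot be reached. The chi-squared comparison would show an imbalance in treatment withdrawal but would not recover outcomes. Multiple imputation helps only as a sensitivity analysis.

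A reader might further infer a loss of power, or a bias in a known direction. Neither can be claimed. No withdrawal rate is given, the documents do not say how missing outcomes were counted in the 23% reference rate, and the Appendix C overlap makes excess withdrawal in the combination arm plausible but does not show it.

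**Conclusion.** The point holds in a limited form. Section 3.10 mixes treatment discontinuation with study withdrawal and can create avoidable missing primary outcomes, which section 4.2 turns into failures. The number affected is unknown and the effect is probably small. Equal withdrawal of 2-5% would cost at most 0.75 of the planned 15 points. Only an assumed imbalance such as 10% against 5% takes off between 1.3 and 2.65 points.

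These figures rest on the planned rates of 23% and 38% and on the assumed q. The upper end, q = 1, supposes that withdrawn participants would abstain and complete CO testing as often as the rest of their arm. Only withdrawals of people who would have accepted contact are avoidable, so the figures overstate the recoverable part if some of the withdrawn had refused. The change is worth making because it is cheap, not because the bias is shown to be large.

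**What to change.** 1. Divide section 3.10 in two. *Treatment discontinuation* takes the drug-related grounds. *Study withdrawal* is kept for the participant's own refusal of further contact, or a clinician's judgement that follow-up contact itself is against the participant's interest.
2. State that stopping study medication does not end the 3-, 6- and 12-month calls or the 6- and 12-month CO tests.
3. Score participants who stop medication on their observed CO-verified outcome. Keep missing = smoker for those who refuse contact or cannot be reached after the section 3.8 attempts.
4. Report, per arm, how many were scored as smokers because contact ended under 3.10. Place this beside the discontinuation summary already planned in 4.2, separate from loss to follow-up.
5. Do not re-contact anyone already withdrawn. Include them in the count in item 4 and treat their outcome as missing in the multiple-imputation sensitivity analysis, which the SAP should carry over from the protocol.

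The cost is one wording amendment, a note to follow-up staff, one extra table row, and a few calls and CO tests for people who stop medication and accept contact. The SAP describes recruitment as complete, so items 1 to 3 help only participants still in follow-up. Items 4 and 5 need no new data from participants.

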### 3.11 End of Trial

Upon the completion of the trial, participants will be requested to handover any remaining medications to the nearest community pharmacy for safe disposal (via The National Return and Disposal of Unwanted Medicines [RUM] program). Participants will also be guided to their community pharmacist and Quitline for support on how to stay 'smoke-free'.

### 3.12 Reimbursement

Participants will be compensated for travel expenses they incur for follow-up visits (e.g. travel for CO testing including parking expenses, mileage within 20km from the testing site and public transport fares). In addition to this, participants will be given a remuneration of \$50 for travel to the hospital or other testing site if a CO breath test is required at the twelve-month follow-up.

## 4. Statistical Considerations

### 4.1 Sample Size

To show a difference of 15% in continuous abstinence between study arms (based on continuous abstinence rate of 23% in varenicline trials) at the 5% level of significance with 80% power, we will need 160 subjects per arm. i.e. 320 participants in total from the six hospitals, , 160 in each of the study arms. The primary analysis will be intention to treat (ITT) and lost to follow-up participants will be regarded as smokers.

### 4.2 Data Analysis

Data will be stored in a suitable database (e.g. REDCap™, ACCESS™) and exported for analysis in Statistical Package for Social Sciences (SPSS) (version 23.0; IBM, Armonk, NY) and Stata (ver 15, StataCorp, College Station, TX). As recommended by the Russell Standard, all randomised patients will be accounted for in the intention to treat (ITT) analysis. Participants with missing outcomes at follow-up or whose self-reported abstinence was not biochemically validated will be considered as smokers. Sensitivity analyses using multiple imputation methods will also be carried out. Deceased participants will be excluded from

analyses. In a supportive analysis of the primary efficacy endpoint, an analysis will also be conducted on the per protocol set, which excludes patients with any major protocol deviations.

Logistic regression analyses will be used to examine the efficacy of intervention on the primary outcome, after testing homogeneity between hospitals using a random effects meta-analysis. In the event of heterogeneity, a more robust model incorporating clustering by hospital will be fitted. The effect of intervention on continuous abstinence at 6 months will be tested in pre-specified subgroups (per hospital, nicotine dependence, highly motivated versus moderately motivated smokers and men versus women) using models fitted for each subgroup containing main effects for intervention and subgroup and an interaction between them. Statistical significance will be considered at a two-sided p value of 0.05.

All randomised participants who take at least one dose of the treatment medications will be included in the safety analysis. A chi-squared test will be done to compare the frequency of treatment withdrawal between the treatment and comparator arms. The number of participants discontinuing treatment prematurely for any reason will be summarised by treatment group and by reasons for discontinuation.

The incidence of all suspected adverse events will be summarised by treatment group under the following categories: type, severity, action taken and outcome. Severity of adverse events will be reported using the CTEAE grading scale (v5.0). The causality of the adverse events will be determined using the Noranjo algorithm.

## 5. Ethics

The trial will be conducted in compliance with the protocol, the principles of Good Clinical Practice (GCP), the National Health and Medical Research Council's (NHMRC) National Statement on Ethical Conduct in Human Research (updated 2015) and the Australian Code for the Responsible Conduct of Research (2018). Ethics committees of participating hospitals and Monash University will review and approve the study. A trained RA will approach each patient at the bedside with a plain language statement, confirm eligibility and obtain written informed consent.

Both varenicline and NRT have well established safety when used in appropriate cases. However, participant safety may still be a concern. Any potential concerns regarding eligibility will be discussed with the treating medical team. Participants in both arms will be closely monitored for any adverse effects.

## 6. Data Safety and Monitoring Board

A three-member independent data safety and monitoring board (DSMB) and study statistician will be set up for reviewing any adverse effects reported in the trial. It acts as an external review committee to ensure the safety of study participants and protect the scientific integrity of the trial. The DSMB regularly reviews trial safety and outcome data and makes recommendations regarding the continuation of the trial based on these data. All serious adverse events (SAEs) will be adjudicated by an end point evaluation committee, which reviews documentation related to the SAE and decides regarding its potential causal

641 relationship with the study drug. Suspected SAEs are also reported as required to the ethics  
642 committee of the hospital which enrolled the participant, the research ethics committee of  
643 Monash University, and to the study sponsor. In the event of any serious adverse events or if  
644 there are any safety concerns, treatment will be discontinued in consultation with the treating  
645 medical team and end point evaluation committee. Any support necessary to those affected  
646 or concerned will be provided independent of the study.

647

648

## Appendix A

### List of contraindications and precautions for the use of varenicline and NRT lozenges

|                     | Contraindications                                                                                                                                                                             | Precautions                                                                                                                                                                                                                                                                                                                                                                                                            |
|---------------------|-----------------------------------------------------------------------------------------------------------------------------------------------------------------------------------------------|------------------------------------------------------------------------------------------------------------------------------------------------------------------------------------------------------------------------------------------------------------------------------------------------------------------------------------------------------------------------------------------------------------------------|
| Varenicline  | 

- Hypersensitivity to the active substance or any excipients

                                                                                  | 

- Irritability

- Depression

- History of psychiatric illness

- Predisposition to seizures (including conditions that may lower seizure threshold)

- History of cardiovascular disease

- Renal Impairment

- Pregnancy

- Breastfeeding

                                                                           |
| NRT Lozenges | 

- Non-smokers

- Phenylketonuria

- Hypersensitivity to nicotine or any other excipients

- Children <12 years of age

 | 

- Hemodynamically unstable patients i.e. serious arrhythmias, myocardial infarction, stroke, cerebrovascular disease

- Pheochromocytoma

- Uncontrolled hypertension

- Diabetes mellitus

- Renal or hepatic impairment

- Sodium restricted diets

- Pregnancy

- Breastfeeding

- Gastrointestinal disease

 |

## Appendix B

### List of drug interactions of varenicline and NRT lozenges:

|                                                                                                                                                                                                                                                                                                                                                                                              | Varenicline                                                                                                                                                                                                                                                                                                                                                                                    | NRT lozenges                                                                                                                                                |
|----------------------------------------------------------------------------------------------------------------------------------------------------------------------------------------------------------------------------------------------------------------------------------------------------------------------------------------------------------------------------------------------|------------------------------------------------------------------------------------------------------------------------------------------------------------------------------------------------------------------------------------------------------------------------------------------------------------------------------------------------------------------------------------------------|-------------------------------------------------------------------------------------------------------------------------------------------------------------|
| Interactions                                                                                                                                                                                                                                                                                                                                                                          | 
No clinically meaningful drug interactions have been identified
 
Alcohol → limited clinical information on a potential interaction between alcohol and varenicline. Increased intoxicating effects of alcohol have been reported by patients taking varenicline. Drinking alcohol may increase the risk of experiencing neuropsychiatric events during treatment with varenicline
 | 
No clinically relevant interactions between NRT and other drugs have been established but nicotine may enhance the haemodynamic effect of adenosine.
 |
| 
Tobacco smoke may induce the metabolism of drugs that are catalysed by CYP 1A2 and thus when a person stops smoking this may result in slower metabolism and a subsequent rise in blood levels of these drugs. Such drugs may need dose adjustments at the smoking cessation (theophylline, imipramine, clomipramine, insulin, clozapine, olanzapine, fluvoxamine and caffeine) (15).
 |                                                                                                                                                                                                                                                                                                                                                                                                |                                                                                                                                                             |

